# Influence of macrolide maintenance therapy and bacterial colonisation on exacerbation frequency and progression of COPD (COLUMBUS): Study protocol for a randomised controlled trial

**DOI:** 10.1186/1745-6215-13-82

**Published:** 2012-06-09

**Keywords:** COPD, COPD exacerbation, Macrolide antibiotics, Long-term treatment, Antibiotic resistance

## Abstract

**Background:**

Chronic obstructive pulmonary disease (COPD) is characterised by progressive development of airflow limitation that is poorly reversible. Because of a poor understanding of COPD pathogenesis, treatment is mostly symptomatic and new therapeutic strategies are limited. There is a direct relationship between the severity of the disease and the intensity of the inflammatory response. Besides smoking, one of the hypotheses for the persistent airway inflammation is the presence of recurrent infections. Macrolide antibiotics have bacteriostatic as well as anti-inflammatory properties in patients with cystic fibrosis and other inflammatory pulmonary diseases. There is consistent evidence that macrolide therapy reduces infectious exacerbations, decreases the requirement for additional antibiotics and improves nutritional measures. Because of these positive effects we hypothesised that maintenance macrolide therapy may also have beneficial effects in patients with COPD who have recurrent exacerbations. The effects on development of bacterial resistance to macrolides due to this long-term treatment are unknown. Until now, studies investigating macrolide therapy in COPD are limited. The objective of this study is to assess whether maintenance treatment with macrolide antibiotics in COPD patients with three or more exacerbations in the previous year decreases the exacerbation rate in the year of treatment and to establish microbial resistance due to the long-term treatment.

**Methods/design:**

The study is set up as a prospective randomised double-blind placebo-controlled single-centre trial. A total of 92 patients with COPD who have had at least three exacerbations of COPD in the previous year will be included. Subjects will be randomised to receive either azithromycin 500 mg three times a week or placebo. Our primary endpoint is the reduction in the number of exacerbations of COPD in the year of treatment.

**Discussion:**

We investigate whether long-term therapy with macrolide antibiotics can prevent exacerbations in patients with COPD. Additionally, our study aims to assess the effect of long-term use of macrolide on the development of antimicrobial resistance and on inflammatory parameters related to COPD. We believe this study will provide more data on the effects of macrolide treatment in patients in COPD and will add more knowledge on its working mechanisms.

**Trial registration:**

http://www.clinicaltrials.gov NCT00985244

## Background

Chronic obstructive pulmonary disease (COPD) is generally accepted to become one of the major health problems in the western worlds in the following years. The main issue is the progressive character of the disease, which is characterised by an ongoing development of non-reversible airflow limitation.

COPD imposes a substantial burden on health-care systems worldwide, as the disease is a major cause of morbidity, mortality, reduced health status and a common cause of medical hospital admission [1]. Because of a poor understanding of COPD pathogenesis, treatment is mostly symptomatic and new therapeutic strategies are limited. One of the known causes of COPD is long-term exposure to noxious particles or gasses. Particularly cigarette smoking is one of the main causes of development of COPD [2]. All smokers show evidence of lung inflammation, but smoking-induced lung injury is variable and appears to be amplified only in a minority of long-term tobacco smokers, suggesting that superimposed processes are the final determinants of COPD development [3,4]. There is a direct relationship between the severity of the disease and the intensity of the inflammatory response [3,4]. Thus, excessive inflammation is likely the key to susceptibility. Inflammation persists long after patients have stopped smoking. The cause of this persistent airway inflammation is unknown although recurrent airway infections seem to play a role in this process.

Macrolide antibiotics have bacteriostatic as well as anti-inflammatory properties [5-7]. The anti-inflammatory capacities of macrolides were firstly established in pulmonary diseases as diffuse panbronchiolitis, a progressive inflammatory disorder of the airways found almost exclusively in Japan [7]. The introduction of long-term macrolide therapy has resulted in dramatic improvements in survival, with 5-year survival rates increasing from 63 to 92% [7,8]. Significant symptom reduction and improved pulmonary function have also been achieved [9-12]. The mechanism of action is thought to be due to immune modifying effects rather than direct antimicrobial activity. Clinical improvement has been reported independent of the presence or absence of chronic airway infection [9] and with antibiotic levels below the minimum inhibitory concentrations of several pathogenic bacteria [13].

Also in patients with cystic fibrosis who are colonised with *Pseudomonas aeruginosa*, macrolide therapy had lead to improvement in forced expiratory volume in 1 s (FEV_1_) and forced vital capacity (FVC), a reduction in exacerbation rate, a reduction in hospital days and days of intravenous antibiotic use, delaying time until the first exacerbation and reducing number of additional courses of antibiotics [14-19]. There is consistent evidence that macrolide therapy reduces infective exacerbations, decreases the requirement for additional antibiotics and improves nutritional measures in patients with cystic fibrosis. A Cochrane review of macrolide therapy concluded that treatment with azithromycin had a small but significant effect on pulmonary function in patients with cystic fibrosis [20].

Although currently the use of maintenance antibiotic treatment in COPD, other than for treating infectious exacerbations COPD, is not recommended by the GOLD report [21]. Several studies have been conducted to assess the effect of long-term therapy with macrolide antibiotics in patients with COPD [22-24]. The results of these studies are conflicting; however some suggest that macrolide antibiotics may become a valuable therapeutic option for COPD patients in preventing exacerbations.

There are essential differences between the different macrolides . From previous studies on macrolide antibiotics it seems that azithromycin is the most potent drug pharmacodynamically [25]. In contrast with erythromycin and clarithromycin, it has a better intracellular uptake, a slower release from cells and a more extensive tissue distribution for a longer lasting effect after cessation of therapy [25,26]. Azithromycin also is known for its mild side effects in comparison with erythromycin [26-29]. Apart from that, in contrast to former studies with macrolides in COPD [22-24] azithromycin can be given on a three times weekly base.

In this randomised placebo controlled trial our main aim is to assess whether maintenance treatment with three times weekly azithromycin in COPD patients with three or more exacerbations in the previous year can decrease the exacerbation rate in the year of treatment and to study the effect of this treatment on microbial resistance.

## Methods

The study is designed as a prospective randomised double-blind placebo-controlled single-centre trial in the department of respiratory medicine in the Amphia Hospital Breda, The Netherlands. Length of study is determined at a period of 3 years, of which 2 years will be spent on patient inclusion and 1 year on treatment. The end of the study is defined by the last visit of the last included subject.

### Patient selection

All patients with COPD who have had three or more exacerbations in the previous year will be asked to participate in the study.

An exacerbation of COPD is defined by a (sub)acute increase of pulmonary symptoms like dyspnoea, coughing, increased sputum volume with or without purulence, for which the patient has consulted a general practitioner (GP) or a respiratory physician, or for which the patient has been admitted to the hospital. The health care professional has judged the symptoms to be in such a degree that treatment was given with systemic steroids and/or a course of antibiotics.

The patients will be recruited from the outpatient department. To assess whether the patient fulfils the criteria for study participation the study subjects’ GP will be contacted to review the patient chart and medication use. The hospital charts will be reviewed as well by the investigator.

### Inclusion criteria

Diagnosis of COPD according to GOLD criteria (FEV1/FVC < 70%), classification into GOLD I (FEV1 80-100% predicted), GOLD II (FEV1 50-80% predicted), GOLD III (FEV1 30-50% predicted) or GOLD IV (FEV1 ≤ 30% predicted).

Age ≥ 18 years.

Three or more exacerbations of COPD in the preceding year of inclusion for which a course of systemic steroids and/or antibiotics therapy was started.

Clinically stable during 1 month. Patients have to be free of COPD exacerbation or respiratory tract infection within a month prior to involvement in the study and in this period they should not have received antibiotics or a course of high doses of systemic steroids defined as more than 10 mg of prednisone a day.

Informed consent.

### Exclusion criteria

Use of antibiotics or a course of high doses of systemic steroids defined as more than 10 mg of prednisone a day within a month prior to involvement in the study.

Addition of inhalation steroids to the patient’s therapy regimen within 1 year prior to study inclusion. Adding inhalation steroids 1 year before trial inclusion can influence the outcome of exacerbation frequencies.

Pregnant or lactating women.

Allergy to macrolides.

Liver disease (alanine transaminase and/or aspartate transaminase levels two or more times the upper limit of normal).

Asthma, defined as episodic symptoms of airflow obstruction which is reversible with bronchodilators, assessed with lung function testing.

Bronchiectasis. A CT scan (1 mm coupes) was performed in all patients to exclude bronchiectasis. Criteria of the BTS guideline Bronchiectasis (non-CF) are used for radiologic definition of bronchiectasis [30].

Malignancy of any kind for which the subject is under treatment or is being monitored as part of follow up after treatment.

Heart failure. A patient is excluded when having clinical signs of heart failure and a cardiac function defined as a left ventricular ejection fraction of less than 45% confirmed by echocardiography or single photon emission computed tomography (SPECT) scan.

Use of drugs that can adversely interact with macrolides and for which therapeutic monitoring cannot be undertaken, e.g. ergotamine derivatives.

### Intervention

Subjects will be randomised to receive either azithromycin 500 mg three times a week or placebo during a 1-year period. During this year subjects will be followed at the outpatient department at 3, 6, 9 and 12 months after initiating the study. During these visits the following tests will be performed according to the flowchart (Table 1):

Lung function testing

Sputum sample collection

Peripheral blood collection

Throat swab

Rectal swab

DS14 questionnaire for assessment of type D personality (only on day 1 and month 12)

Hospital Anxiety Depression Scale (HADS)

12-Item Short Form Health Survey (SF-12)

St. George’s Respiratory Questionnaire (SGRQ).

**Table 1 T1:** Overview of outpatient department visits and tests

	**Day 1**	**Month 3**	**Month 6**	**Month 9**	**Month 12**	**Other***
Informed consent	X					
Blood works	X	X	X	X	X	X
Microbiology	X	X	X	X	X	X
Lung function testing	X	X	X	X	X	
Rectal swab	X		X		X	
Questionnaires	X	X	X	X	X	X

In case of exacerbation subjects have the choice to get treatment from their general practitioner or to visit the hospital to be seen by the investigator. Either way sputum and peripheral blood will be collected for immunological and microbiological investigations. Also the subjects with an exacerbation will be asked to complete the SF-12, HADS and SGRQ.

### Type D personality

The Type D Scale (DS14) will be administered to assess Type D personality [31]. This 14-item questionnaire comprises two subscales, Negative Affectivity and Social Inhibition, each consisting of seven items. Items are answered on a 5-point Likert scale, ranging from 0 (false) to 4 (true). A standardised cutoff score ≥ 10 on both subscales is used to classify individuals with a Type D personality [32]. A previous study confirmed that it is the interaction of both traits, rather than the single traits, that incurs an increased risk of adverse health outcomes [32]. Both of the DS14 subscales of Negative Affectivity and Social Inhibition have good internal validity (Cronbach’s *α* = 0.88/0.86), are stable over a 3-month period (*r* = 0.82/0.72), and are independent of mood and health status [31].

### Depressive and anxious symptomatology

The Dutch version of the Hospital Anxiety and Depression Scale (HADS) will be used to assess depressive and anxious symptomatology [33,34]. Both subscales consist of seven items that are answered on a 4-point Likert Scale, ranging from 0 to 3. A cutoff score of ≥ 8 for each subscale represents probable clinical levels of anxiety and depression [35]. Test-retest reliabilities over a 3-week period for the subscales and the total scale are good (0.86 < *r* < 0.91) [34]. The dimensional structure and reliability of the HADS has been shown to be stable across medical settings and age groups [24,34].

### Health status

The Dutch version of the Short-Form Health Survey12 (SF-12) will be administered to assess generic health status [36,37]. This generic instrument measures overall physical and mental health status, as indicated by the Physical Component Scale Summary (PCS) and the Mental Component Summary (MCS) scores [38]. According to standard scoring procedures, all scale scores will be standardised to the general US population (range 0–100, mean = 50, SD = 10), with higher scores indicating better functioning. The SF-12 has been demonstrated to be a reliable and valid instrument [37].

### Health-related quality of life

Disease specific health related quality of life will be measured by the total score on St. George’s Respiratory Questionnaire (SGRQ) [39]. Three component scores are calculated: symptoms, activity, and impacts (on daily life), and a total score. Total scores range from 0 to 100, with lower scores indicating improvement.

### Study endpoints

#### Primary study outcome

Reduction in the number of exacerbations of COPD in the year of treatment.

### Secondary study outcome

Measurement of lung function parameters and 6 min walking distance.

Assessment of presence of type D personality by DS14 questionnaire.

Disease specific health related quality of life measured by St. George’s Respiratory Questionnaire (SGRQ).

Generic health status measured by the 12-Item Short Form Health Survey (SF-12).

Indication of anxiety and depression by Hospital Anxiety Depression Scale (HADS).

Microbiology: Sputum specimens will be cultured. Polymerase chain reaction (PCR) in sputum and serology in serum for viral and atypical microorganisms will be performed. The rectal swabs will be tested for change in rectal flora as a result of maintenance azithromycin.

Measurement of inflammatory markers in serum [erythrocyte sedimentation rate (ESR), C-reactive protein (CRP), pro-adrenomedullin, (pro-ADM), interleukin-6 and cytokine profiles of T-helper 1, T-helper 2 and T-helper 17 cells].

Decrease in percentage of clinical versus outpatient department exacerbations.

Difference in treatment effect between subjects with and without steroid maintenance therapy as hypothesis-generating secondary analysis.

Adverse events of treatment. Symptoms that are believed to be (possibly) related to therapy will be reviewed at the outpatient department. If a patient has an adverse event that is thought to be drug related and that does not resolve, then the patient will be withdrawn from the study. There will be no routine ECG screening since azithromycin (in contrast to erythromycin) is much less likely to be a cause of a prolonged QTc interval.

Length of hospital stay.

Time till first exacerbation.

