### Sample size and statistical analysis

#### Power calculation and number of study subjects

This calculation starts with the assumption that the number of exacerbations follows a pure Poisson distribution with a mean rate of 3 per subject per year in the placebo group. A 50% reduction in this rate is considered to be clinically relevant. Hence, in the active treatment group the mean exacerbation rate is set at 1.5 per subject per year. With 33 subjects per treatment group followed up for 1 year, this reduction is detectable with 90% power, given a test size alpha of 0.05 (2-sided).

However, the assumption of a pure Poisson distribution may be too strong. In fact, it is plausible that in this case a zero-inflated Poisson process may be present (the outcome of zero exacerbations has a higher probability than that following from a pure Poisson distribution). In addition there is a risk of overdispersion (the variance is larger than the mean). These phenomena may be expected to have a negative (not exactly quantifiable though) effect on the power of the study.

In order to reasonably compensate for the risk of a too low power and for subjects dropping out within one year follow-up, the number of subjects will be augmented by 40%, so that the sample size is set at 46 subjects per treatment group.

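### The percentage of clinical versus outpatient exacerbations is taken only among exacerbations that occur, so it misses a proportional benefit and can rise while admissions fall

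*Protocol article*

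**What the plan says.** Under Secondary study outcome, the protocol article names the quantity and the direction that counts as benefit: "Decrease in percentage of clinical versus outpatient department exacerbations". That section lists no count or rate of admissions.

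The primary outcome is "Reduction in the number of exacerbations of COPD in the year of treatment". The section on power assumes a "pure Poisson distribution with a mean rate of 3 per subject per year in the placebo group" and adds that "in the active treatment group the mean exacerbation rate is set at 1.5 per subject per year".

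Under Statistical analysis, the primary rate is analysed by Poisson regression with log time under treatment as offset and, where needed, a scale correction for overdispersion. The article names no analysis for the percentage. That may stand in the full protocol or the SAP and is not held against the plan.

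**The concern.** The trial expects the drug to change how many exacerbations there are. A percentage of exacerbations uses that number as its denominator, so the two arms are compared on sets of events that treatment has itself selected. Patients who stay free of exacerbations are the clearest successes, yet they contribute nothing.

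The sign of the difference in percentage therefore need not agree with the sign of the effect on admissions. No admission rate is listed, so this item is the only listed outcome on how often exacerbations lead to hospital. A fall in admissions could be reported as no effect, or as a worsening, on an outcome whose stated success is a decrease.

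**Working it through.** **Stated figures.** The article gives no number for this outcome, so there is nothing to reproduce for it directly. The size used below, 46 per group, follows from the article: 33 × 1.4 = 46.2. The 33 itself does not come out of the usual log-rate-ratio formula under pure Poisson: (1.960 + 1.282)² × (1/3 + 1/1.5) / (ln 2)² = 21.9, or 22 per group. That is a separate matter and does not enter this point.

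**Inputs**
- Total rate: 3 per year on placebo and 1.5 on active, a rate ratio of 0.5 (power calculation).
- 46 patients per group, each followed for one year.
- Clinical exacerbations are read as those leading to admission.
- Admitted share on placebo, p: not in the documents. 20% is assumed, with a range of 10% to 40%.

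**Who drops out of the percentage.** Under the article's Poisson rates, the chance of no exacerbation is exp(−3) = 5.0% on placebo and exp(−1.5) = 22.3% on active. That is about 46 × 0.050 = 2 and 46 × 0.223 = 10 patients. Expected events are 46 × 3 = 138 and 46 × 1.5 = 69.

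**Formula.** The percentage is admitted rate / total rate. Hence

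percentage on active = p × (rate ratio for admissions) / (rate ratio for total).

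It is unchanged when the two rate ratios are equal. It is higher when admissions fall by a smaller proportion than the total, and lower only when they fall by a larger one.

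**With the total halved and p = 20%** (placebo 0.60/3.0 = 20%):

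| Admissions on active | Rate per year | Percentage on active |
|---|---|---|
| down 70% | 0.18 | 0.18/1.5 = 12% |
| down 50% | 0.30 | 0.30/1.5 = 20% |
| down 30% | 0.42 | 0.42/1.5 = 28% |
| down 25% | 0.45 | 0.45/1.5 = 30% |
| unchanged | 0.60 | 0.60/1.5 = 40% |

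**Range of p.** With admissions down 25%, shares of 10, 20, 30 and 40% become 15, 30, 45 and 60%. With admissions down 70%, they become 6, 12, 18 and 24%. With admissions halved, they do not change. Reading the item as a ratio of admitted to non-admitted gives the same directions. At p = 20% the placebo ratio is 0.60/2.40 = 0.25, against 0.30/1.20 = 0.25 (halved), 0.45/1.05 = 0.43 (down 25%) and 0.18/1.32 = 0.14 (down 70%).

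**How often each result would be seen.** Simulation with 20,000 trials, 46 per group, Poisson counts, total halved, two-sided 5%. The percentage is tested on pooled events and admissions by the log rate ratio. The three columns on the right show the share of trials with a significant result.

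| True fall in admissions | p | Percentage falls | Percentage rises | Admission rate falls |
|---|---|---|---|---|
| 50% | 10% | 2.2% | 2.9% | 31% |
| 50% | 20% | 2.3% | 2.8% | 57% |
| 50% | 30% | 2.5% | 2.7% | 75% |
| 50% | 40% | 2.5% | 2.7% | 86% |
| 30% | 20% | 0% | 26% | 21% |
| 30% | 30% | 0% | 41% | 31% |
| 70% | 20% | 29% | 0% | 91% |
| 70% | 40% | 64% | 0% | 99.7% |

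Under a proportional halving the percentage falls significantly no more often than chance. When it does point the right way (admissions down 70%), the admission rate still finds the effect far more often.

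**The case against.** The best defence is that the item asks a different question: whether the mix of exacerbations shifts away from admission. No change is then the correct answer to a proportional effect, and the overall benefit is already covered by the primary rate analysis. This stands to the extent that the defect is confined to one secondary outcome. It does not rescue the item as a measure of benefit. The article presents a decrease as the outcome sought, and a rise can come solely from preventing milder exacerbations.

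It is also fair to say that the article does not state whether a formal test is planned. The point above concerns the chosen quantity, which no choice of test would alter.

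Three stronger readings are tempting and are not supported:

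- A reader might infer that the percentage can never show the planned benefit. The power section sets the 50% reduction on the total rate and does not say how it divides by setting. If admissions fall by more than half, the percentage does decrease.
- A reader might infer that "Length of hospital stay" has the same fault. The article does not say that it is restricted to admitted patients. Total days per randomised patient fits the wording equally well, so nothing is claimed about it.
- A reader might infer that exacerbations treated by the general practitioner are left out of the percentage, since "subjects have the choice to get treatment from their general practitioner" and the label names only two settings. Outpatient may simply mean not admitted. The label is unclear, but exclusion is not stated.

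**Conclusion.** The concern holds in this limited form. The percentage conditions on events that treatment is meant to prevent. It does not register a proportional reduction, moves in the wrong direction when admissions fall by less than the total, and decreases only when they fall by more. With the article's rates and an assumed 20% admitted share, the same halving of the total can appear as 20% versus 12%, 20% or 30%, according to whether admissions fall by 70%, 50% or 25%.

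The directions are algebraic and do not depend on the assumed share. The sizes do, and the frequencies also assume Poisson counts, full one-year follow-up and independent events. The article itself expects overdispersion, which would lower the power of both tests and make a pooled-event test too liberal. The consequence is a possibly wrong-signed conclusion on one secondary outcome. The primary result is untouched.

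**What to change.** Make the secondary outcome the rate of hospitalised exacerbations per patient-year in all randomised patients. Report it as a rate ratio with 95% confidence interval from the Poisson model already planned for the primary outcome, with its time offset and overdispersion correction. Report beside it the rate of non-hospitalised exacerbations, general practitioner and outpatient together, which also settles where events treated by the general practitioner belong. Keep the percentage as a description by arm, without a test and without a direction of success.

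The data should already be available, because admission is part of the exacerbation definition under Patient selection. The trial is registered, approved and recruiting, so the change needs an amendment to one secondary outcome, best made before unblinding. Power for admissions is modest: for a true halving, about 31%, 57%, 75% and 86% at admitted shares of 10, 20, 30 and 40%. Expected admissions over both arms range from 46 × (0.30 + 0.15) = 21 to 46 × (1.20 + 0.60) = 83, so at the low end the estimate and its interval should carry the message and the covariate list may need shortening.

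### The inpatient percentage describes the mix of the remaining exacerbations, not the effect on admissions; an admission rate per patient-year should be added

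*Protocol article*

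**What the plan says.** Under Secondary study outcome, the protocol article lists "Decrease in percentage of clinical versus outpatient department exacerbations", so a decrease is the favourable direction. The same list contains "Length of hospital stay" and does not say whether this is counted per admission or per patient. It contains no number or rate of admitted exacerbations and no time to first admission.

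The primary outcome is the number of exacerbations in the treatment year. The definition under Patient selection covers every place of care alike: events "for which the patient has consulted a general practitioner (GP) or a respiratory physician, or for which the patient has been admitted to the hospital". Under Intervention, for an exacerbation during the trial, "subjects have the choice to get treatment from their general practitioner or to visit the hospital to be seen by the investigator".

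The planning assumptions are "a mean rate of 3 per subject per year in the placebo group" and "A 50% reduction in this rate is considered to be clinically relevant". The Statistical analysis section sets out a Poisson regression with a log time offset and a scale correction for overdispersion, for the total exacerbation rate.

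**The concern.** A percentage of exacerbations has a denominator that arises after randomisation, and here that denominator is the primary outcome itself. If the drug works as planned, the denominator shrinks. Whether the percentage moves, and in which direction, then depends on whether admissions fall proportionally more or less than other exacerbations. The number of admissions prevented does not decide it.

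The stake is interpretation. A real fall in admissions could be reported as no difference, or as a larger inpatient share on azithromycin, with no listed outcome beside it giving the randomised comparison of admissions per patient-year.

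**Working it through.** **Inputs from the document.** Rates of 3 and 1.5 exacerbations per patient-year, 46 patients per group, 1 year. Expected exacerbations: 46 × 3 = 138 on placebo and 46 × 1.5 = 69 on active treatment.

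**Input not in the document.** The share of placebo exacerbations that lead to admission, p. It is assumed to be 20%, with a range of 10% to 40%.

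**The plan's own figure.** The increase from 33 to 46 reproduces (33 × 1.4 = 46.2). The 33 itself does not follow from the usual Poisson formula: (1.96 + 1.2816)² × (1/3 + 1/1.5) / (ln 0.5)² = 21.9, or 22 per group. The stated number is thus larger than the formula needs, and the difference has no bearing on this point.

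**Step 1, the algebra.** Let r_in and r_out be the rate ratios for admitted and other exacerbations. The share on active treatment is

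p·r_in / (p·r_in + (1 − p)·r_out).

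This equals p when r_in = r_out, whatever p is. It is below p only if r_in < r_out and above p if r_in > r_out, even when r_in is well below 1.

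**Step 2, the numbers at p = 20%.** Placebo has 27.6 admissions among 138 exacerbations.

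| Fall in admitted / other events | Active admissions | Active total | Share, placebo to active |
|---|---|---|---|
| 50% / 50% | 13.8 | 69.0 | 20% to 20% |
| 30% / 55% | 19.3 | 69.0 | 20% to 28% |
| 20% / 50% | 22.1 | 77.3 | 20% to 28.6% |
| 50% / 25% | 13.8 | 96.6 | 20% to 14.3% |
| 60% / 47.5% | 11.0 | 69.0 | 20% to 16% |

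The first row gives no difference at any p from 10% to 40%. Rows 2 and 3 show the percentage rising while admissions fall. Rows 4 and 5 show that it does register a benefit when admissions fall proportionally more.

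**Step 3, patients without an exacerbation.** Under the Poisson planning rates these are exp(−3) = 5.0% of placebo patients (2.3 of 46) and exp(−1.5) = 22.3% of active patients (10.3 of 46). They add nothing to numerator or denominator, so the percentage does not compare the groups as randomised.

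**Step 4, exacerbations treated by the general practitioner.** The outcome names two categories and does not place these. If half of the non-admitted events went to the general practitioner and were left out, a 20% share would become 0.20 / (0.20 + 0.40) = 33.3% with no change in severity.

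**Step 5, what an admission rate would show.** Under a uniform halving the admission rate ratio is 0.50 at any p. Its power, with A0 and A1 expected admissions, is Φ(ln 2 / √(1/A0 + 1/A1) − 1.96):

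| Assumed p | A0 vs A1 | Power |
|---|---|---|
| 15% | 20.7 vs 10.35 | 44% |
| 20% | 27.6 vs 13.8 | 56% |
| 25% | 34.5 vs 17.25 | 65% |
| 40% | 55.2 vs 27.6 | 84% |

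At p = 20% the standard error of the log rate ratio is √(1/27.6 + 1/13.8) = 0.330, so an estimate of 0.50 carries a 95% interval of about 0.26 to 0.95. Overdispersion, which the protocol expects, would widen it.

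**The case against.** The strongest defence is that the percentage answers a different and legitimate question: are the exacerbations that still occur milder? No change under a uniform reduction is then the right answer, and frequency is covered by the primary outcome. This stands, and it is why the percentage is worth keeping. It does not make the percentage a measure of the effect on admissions. A reader can recover that effect only by multiplying the exacerbation rate ratio by the ratio of the two percentages (0.5 × 28/20 = 0.7 in row 2). That requires every exacerbation to be in the denominator and gives no confidence interval.

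Four stronger readings are tempting, and the document does not support them.

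- **That this is the only outcome touching severity.** Length of hospital stay is also listed. Counted as total days per patient it would reflect fewer admissions; counted per admission it would not. The article does not say which.
- **That the percentage misses any halving of admissions.** It does so only if other exacerbations halve as well.
- **That the trial would probably show significant harm.** With an assumed 25% share and falls of 20% and 60%, the share goes from 25% to 40% and a simple two-proportion test on expected counts gives p = 0.026. But that split, the share and the test are all constructed for illustration. In that case the mix really has shifted, and the percentage reports it correctly.
- **That treatment by the general practitioner biases the comparison.** The trial is randomised and double-blind, and nothing suggests that the choice of care differs by group. What is shown is an unclear category.

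Reading clinical as inpatient is also an interpretation, though the contrast with the outpatient department makes it the natural one. An article may leave the handling of patients without events and of general-practitioner events to the full protocol. The choice of a percentage as the outcome is stated in the article itself.

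**Conclusion.** The point holds in a limited form. The secondary outcome measures the composition of the remaining exacerbations, and no listed outcome gives admitted exacerbations per patient-year. That the percentage stays flat under a uniform halving, and rises when admissions fall proportionally less than other events, is algebra and needs no outside figure. The sizes shown rest on the planning rates, an assumed admitted share of 10% to 40%, and illustrative splits of the effect. The 5% and 22% of patients without events rest on the pure Poisson assumption.

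This concerns one secondary outcome. It does not affect the primary analysis or its conclusion. The change is worth making because it is cheap and supplies a randomised comparison that would otherwise be absent.

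**What to change.** Add, as the between-group comparison, the rate of exacerbations with hospital admission per patient-year in all randomised patients, counting zero for those never admitted. Analyse it as a rate ratio with a 95% confidence interval, using the Poisson regression with log time offset and overdispersion correction already planned for the primary outcome.

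Use a reduced covariate set if events are few. The primary model has treatment plus seven covariates, so at least eight coefficients. At a 25% share there would be 34.5 + 17.25 = 51.75 admissions, about 6.5 per coefficient; at 15% there would be 31.05, about 3.9.

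Keep the percentage as a descriptive measure of mix, state that clinical means admitted, and count exacerbations treated by the general practitioner as non-admitted. State whether length of hospital stay is per admission or per patient.

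The cost is a few lines of outcome wording and one extra model run. Place of treatment is already needed for the stated outcome, so no new data are required. The article reports that the trial is still recruiting, so this can be fixed before unblinding. The drawback is precision: power of about 44% to 84% at shares of 15% to 40%, lower with overdispersion, so the result should be read as an estimate with its interval.
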